### Harms

This trial should be regarded as therapeutic research, as two different treatment strategies are compared. Patients allocated to usual care will receive IBD care as before. There is no additional risk in this group. Patients in the experimental arm will have fewer scheduled encounters with their local IBD team, and blood drawings will be reduced to once every six months. This relatively long interval between two phlebotomies may hinder early recognition of adverse drug reactions, although it is not uncommon for teenagers with quiescent IBD to have only two blood drawings per year. Patients from both groups are instructed to contact the local IBD-team if they experience relapse, or if at any time they want a consultation. The management of relapses is not changed from the current routine practice and is the same for both groups.

In this trial an adverse event will be defined as any undesirable experience occurring to a participant during the study, whether or not considered related to the experimental intervention, including any unscheduled health visit. Adverse events will be collected after the participant has provided consent and enrolled in the study. If an adverse event is experienced within one month after the enrollment visit, the event will be reported as not related to the trial. All adverse events occurring later than one month after enrollment will be recorded. An adverse event that meets the criteria for a serious adverse event between study enrollment and hospital discharge will be reported to the local MEC.

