### Inclusion and exclusion criteria for participants

Approximately 10 % of teenagers with IBD will have a severe disease course and require use of the complete arsenal of available therapies in a limited period of time to maintain remission. We aim to include the other 90 % of teenagers with a more stable disease course.

Eligible patients are those: 10- to 19-years old, with quiescent IBD for more than three months before study enrollment, with IBD diagnosed according to the Porto criteria [24] more than six months before enrollment, who have access to internet, with knowledge of the Dutch language, and with an adult caregiver who is willing to actively support participation.

Potential participants will be excluded from the study if any of the following conditions occur: maintenance treatment with infliximab or adalimumab (for unavoidable frequent contact with health providers); presence of ileostomy or ileoanal pouch (as fCal cut-off is not validated for small bowel feces); or any comorbidity at the time of enrollment that requires hospitalization or frequent blood sampling.

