### Interventions—modifications

Study participants from both groups are instructed to contact their doctor immediately to report clinical deterioration between regular health checks, or if at any time they want a consultation (side effects, other health related questions). Rapid access to specialist care is guaranteed for both groups. All unscheduled health visits (including those at the IBD clinic, general physician and emergency department) and hospital admissions are documented in the study data tracking system and are reported as adverse events. Crosschecking will be done by comparing doctor reported health consumption and patient-reported health consumption.

Study participants can leave the study at any time for any reason if they wish to do so without any consequences. The local principal investigator can decide to withdraw a teenager from the study for urgent medical reasons. Another patient from the same center may then be randomized to enter the study.

Patients withdrawn from the experimental arm of the trial will continue with usual care, outside the scope of this study, as would have happened otherwise. Patients who receive usual care and withdraw from the study will continue to receive usual care as before entering the study.

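### The Harms section labels every first-month adverse event unrelated by rule, conflicts on whether such events are recorded, and ends serious-event reporting at a hospital discharge that outpatients do not share

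*Protocol article*

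**What the plan says.** The Harms section of the protocol article defines an adverse event broadly, "whether or not considered related to the experimental intervention, including any unscheduled health visit". It then gives four rules.

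- **Start of collection:** "Adverse events will be collected after the participant has provided consent and enrolled in the study".
- **Attribution in the first month:** "If an adverse event is experienced within one month after the enrollment visit, the event will be reported as not related to the trial".
- **Recording:** "All adverse events occurring later than one month after enrollment will be recorded".
- **Serious events:** "An adverse event that meets the criteria for a serious adverse event between study enrollment and hospital discharge will be reported to the local MEC".

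A separate rule stands under Interventions—modifications. Unscheduled visits (IBD clinic, general physician, emergency department) and hospital admissions "are documented in the study data tracking system and are reported as adverse events". That rule has no first-month exclusion and no end at discharge.

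The population is described as patients "with quiescent IBD for more than three months before study enrollment". Participant timeline places their assessment for entry at an outpatient appointment, and Retention sets follow-up at 52 weeks.

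**The concern.** Relatedness is a judgement about an individual event. The definition of an adverse event treats it as separate from whether the event counts, but the first-month rule removes the judgement. By the Harms section's own account, usual care carries no additional risk, so harm caused by the strategy can arise only under IBD-live. A rule that turns every early relatedness label into a negative one can therefore err in one direction only, in favour of the experimental arm.

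The recording and serious-event sentences raise a different problem. Ten centers need one rule on which events to record and when reporting to the ethics committee stops. The text gives conflicting answers to the first question and an unusable answer to the second.

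At stake is the credibility of a later statement that fewer scheduled contacts are safe. The Harms section itself concedes that longer intervals between blood samples may delay recognition of adverse drug reactions, and many participants are minors.

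**Working it through.** The plan states no figure on this point, so there is nothing to reproduce. The check sets the passages side by side and adds two shares of time.

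**1. Does the first month include time on the allocated strategy?**
- The clock of the rule starts at the enrollment visit (Harms).
- Randomization follows completion of all baseline measurements (Randomization and masking).
- Some baseline questionnaires are filled in at home, up to one week after enrollment (legend of Fig. 3).
- Assume a delay from enrollment to randomization of 0 to 7 days and a month of about 30 days. Time after allocation is then 30 − 7 = 23 days to 30 − 0 = 30 days.

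Most of the month can therefore lie after allocation.

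**2. Could the strategy act within that time?**
- A stool result enters the flarometer within 24 hours of reception. A high-risk result leads to advice to intensify treatment (Home monitoring of disease activity and treatment algorithm).
- When the first flarometer use is due cannot be seen, because Fig. 3 is not shown. A first use in month one is possible but not established.
- The difference in visit frequency is not an early mechanism. Routine visits are described as three-monthly (Need for a trial), and usual-care patients may have appointments at three and nine months (Participant timeline). On that schedule the arms first differ at about month three.

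Algorithm-driven advice is therefore the one early route that the text supports.

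**3. How much time does the rule cover?**
- Share of follow-up: 1/12 = 8.3%.
- Share of the six-month interim window (Premature termination of the study): 1/6 = 16.7%.

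These are shares of time. No event rate by month is given, so they do not convert into shares of events.

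**4. Are first-month events recorded?**

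| Source | First-month events |
|---|---|
| Harms, collection sentence | Collected from consent and enrollment |
| Harms, attribution sentence | Reported, labelled not related |
| Harms, recording sentence | Recording promised only after one month |
| Interventions—modifications | Unscheduled visits and admissions documented and reported, no time limit |

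The third row does not fit the other three.

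**5. Can hospital discharge close the serious-event window?**
- There is no index admission: participants are in remission and enter at an outpatient visit.
- A participant who is never admitted has no discharge, so the window has no defined end.
- For a participant admitted once, a literal reading puts any serious event after that discharge outside the window.
- Harms does not name the end of the 52 weeks as the limit.

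**6. What do the other rules still catch?**
- Unscheduled visits and admissions at any time enter the data tracking system under Interventions—modifications. That section does not say that they go to the ethics committee.
- A serious event that is neither an admission nor an unscheduled visit depends on the Harms rules alone.
- The interim composite score counts unscheduled visits, emergency visits and admissions. It does not use relatedness, so the not-related label cannot change it. It would lose events only if sites took the recording sentence as an instruction to leave out month one.

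**The case against.** The strongest reply is that little is lost in practice. Unscheduled visits and admissions are documented in both arms throughout, with doctor and patient reports cross-checked. They are also secondary endpoints, and health-care use is asked about at entry and monthly (Outcomes). Even the disputed sentence says that the early event will be reported. The interim comparison is of counts, not attributions, and the monitoring board may ask for further analyses. The primary endpoint, the randomization and the sample size are untouched. Discharge does exist for a participant who is admitted during follow-up.

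All of that stands, and it limits the consequence. Four stronger readings are tempting, and the documents do not support them:

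- **That early harms will be missed altogether.** Visits and admissions are captured under the separate rule, so for other events and for committee reporting the most that can be said is that some may be missed.
- **That the interim score drops the first month.** The section describing the score excludes no period.
- **That fewer scheduled visits already create risk in month one.** The described schedule does not show this.
- **That at least 8.3% or 16.7% of events are affected.** Participants have been quiescent for more than three months, so early events could be fewer than proportional to time.

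The reply does not reach the attribution rule, which no other section corrects. Nor does it supply a common end for serious-event reporting or reconcile the recording sentence with the collection sentence.

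**Conclusion.** The point holds in a limited form. As written, any related event in the first month after enrollment would be misattributed by rule. The protocol conflicts with itself on recording such events, and serious-event reporting to the ethics committee lacks a valid common end, so some serious events may go unreported to it.

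The attribution rule covers 8.3% of follow-up time. The number of events affected cannot be derived from the article. It depends on when the first flarometer result falls, which is not visible, and on early event rates, which are not given. The estimate that 23 to 30 days fall after allocation rests on the assumed delay of 0 to 7 days.

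Between-arm counts of visits and admissions are protected by Interventions—modifications. The interim score is at risk only if sites act on the later-than-one-month sentence. These are rules that the article states, not details left to a fuller document, and correcting them is worthwhile because it is cheap and concerns safety reporting.

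**What to change.** Amend the Harms section as follows:

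1. Delete the sentence that declares first-month events unrelated. Have relatedness judged case by case, whatever the date of the event.
2. Replace the recording sentence with one stating that all adverse events are recorded in both arms from consent and enrollment to week 52 or study exit, in line with Interventions—modifications. The start should not be moved to randomization, because that would narrow the collection period that Harms already sets.
3. Define the window for reporting serious events to the ethics committee as enrollment to the end of the 52-week follow-up or study exit.

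The interim score needs no change of its own once the recording sentence is corrected. The cost is the amendment wording and a few more event forms; the visits and admissions are already being documented.

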### Ethics

The trial will be conducted according to the principles of the Declaration of Helsinki (59th version, October 2008) and in accordance with the Dutch Medical Research Involving Human Subjects Act (WMO). The independent Medical Ethical Committee (MEC) of the University Medical Centre Groningen (Groningen, the Netherlands) has approved the study protocol.

Secondary approval was obtained from the boards of the Academic Medical Centre (Amsterdam), Erasmus Medical Centre (Rotterdam), Haga Hospital (Den Haag), Isala Hospital (Zwolle), Leiden University Medical Centre (Leiden), Medisch Spectrum Twente (Enschede), Rijnstate Hospital (Arnhem), University Medical Centre Utrecht (Utrecht), and VU medical center (Amsterdam) according to the Dutch CCMO External Review Directive 2012 (RET 2012).

Any modifications to the protocol which may impact on the conduct of the study, potential benefit of the patient or may affect patient safety, including changes of study objectives, study design, patient population, sample sizes, study procedures, or significant administrative aspects will require a formal amendment to the protocol. Such amendment will be approved by the MEC prior to implementation and notified to the participating centers.

Written informed consent will be obtained from both parents or legal guardians of all participants younger than 18 years old, and from all teenagers 12- to 19-years old, prior to randomization. The trial is registered in the Dutch Trial Register (http://www.trialregister.nl/trialreg/index.asp) with identification number NTR3759.

## Discussion

This trial will test the use of remission induction therapy delivered according to a web-assisted calprotectin-based treatment algorithm head-to-head against the same treatment based on physician assessment of individual patient characteristics.

We expect that use of IBD-live will result in better disease control, expressed as a lower relapse rate, accompanied by lower costs of disease management as compared to usual care. The number of scheduled outpatient visits is expected to drop by 50 %, unscheduled visits for uncertainty concerning suspected relapse will probably reduce in number, and the number of unscheduled visits for confirmed relapse are also expected to drop by 50 %. The physician’s workload is expected to decrease, while the nurse’s workload is expected to increase. Combined with the expected drop in relapse frequency, this could mean that IBD-live is the dominant strategy in the cost-effectiveness analysis.

### Relevance for practice/implementability

IBD-live care corresponds to the needs and wishes of both patients and clinicians. Unnecessary, but time-consuming visits to the clinic are reduced, while the quality of disease monitoring is maintained or even improved. Scientific societies and patient associations broadly support the concept of tailor-made IBD-management, and health insurance companies are co-financing this scientific project.

If IBD-live care proves to be effective, funding for this type of long-term care will be provided under the Exceptional Medical Expenses Act (AWBZ). The trial will yield information on disease monitoring with fCal, which has hitherto been a gap in both national and international guidelines. Study results will eventually be included in Dutch and international guidelines.

### Additional value of the study

Pediatricians have so far always been reluctant to allow teenagers in the driving seat. Now that reliable non-invasive predictors of relapse have become available, home monitoring may be a feasible concept. If IBD-live care proves to be effective, this would mean a fundamental change in approach.

Treatment intensification in teenagers who are doing well, but who have a high risk of progression to clinically overt relapse, is currently not recommended. Periodically measuring fCal levels may facilitate recognition of preclinical relapse. The trial described in this protocol will allow us to determine whether preemptive treatment of teenagers with increased fCal levels, but who report no complaints, really prevents progression to symptomatic relapse. This could be the second paradigm shift.

### Trial status

Recruitment began on 6 June 2013. It is anticipated that study recruitment will be completed by 30 September 2015, and that the trial will conclude by 30 September 2016.

## Abbreviations

CRP: C-reactive protein
DSMB: Data Safety Monitoring Board
fCal: Fecal calprotectin
IBD: Inflammatory bowel disease
MEC: Medical Ethical Committee
MMAS: Morisky Medication Adherence Scale
PCDAI: Pediatric Crohn’s Disease Activity Index
PUCAI: Pediatric Ulcerative Colitis Activity Index
shPCDAI: Short version of the PCDAI
TNF: Tumor necrosis factor
UMCG: University Medical Centre Groningen
